### The intervention programs

The conceptual framework of the health promotion model will be developed based on phase 1 findings from the qualitative study. Recruitment of women who meet the inclusion criteria will continue until the required sample size is achieved. At this point, all participants will be coded and blindly allocated into one of four intervention groups by the researchers using a permuted block randomization program: (1) biomechanical, (2) psychosocial, (3) multidisciplinary (biomechanical and psychosocial), or (4) control. Based on the design of the randomized controlled trial intervention, the impact of the different intervention programs on musculoskeletal disorders, work ability, and quality of life of the housewives will be evaluated. As shown in Fig. 1, measures will be collected at baseline, after 3 months, and after 6 months of following their respective program.

To implement the content of the three intervention programs, a participatory ergonomic approach will be used. The effectiveness of this approach in ergonomic interventions depends on the ability and active cooperation of participants [29]. The required training content for participants in the psychosocial intervention will be provided following the conceptual framework developed in the qualitative study and the resulting theory. Similarly, for participants in the biomechanical intervention group, the required training will be provided following the conceptual framework derived from the qualitative study and job safety analysis (JSA) method. Finally, the multidisciplinary intervention group will receive the training provided to the psychosocial and biomechanical groups: that is, they will do both interventions. The multidisciplinary groups will receive both of the other two interventions in full.

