After providing the required training programs, the 40 participants in each of the three intervention groups will be divided into 4 subgroups of ten participants. There will be an expert, as a facilitator, who will each manage one of the 12 subgroups, overseen by a coordinator. Subgroup meetings will be held weekly to retrain the materials taught to the group members and discuss the actions taken by the members of the subgroups. The facilitators will be responsible for reviewing the training content provided to the participants in their subgroup, discussing the experiences of and the actions taken by the members of their subgroups, and performing the required assessment during the intervention period. The facilitators of the intervention groups will communicate with each other by forming a social group through virtual networks and face-to-face meetings and share the experiences of their subgroups with each other. The facilitator coordinator will ensure all aspects of the subgroup training and associated interactions are appropriate and intervene if necessary, to reduce any foreseeable risk of harm. The study group evaluators will remain blind to group allocation throughout the intervention, including knowledge of withdrawal from the study.

The facilitators will be provided with training for their role that will include information on how to manage work teams and how to use the risk assessment methods and other tools used in the present study. It will be made clear that the facilitators should not interfere in the participant’s training procedures or in the implementation of the interventions; their purpose is to play a facilitating role based on the principles of participatory ergonomics. In order to ensure the implementation of the interventions, reminder messages will sent to the participants on a weekly basis through virtual network. After the final evaluation and comparisons of the three intervention groups, the participants in the control group also will receive the most effective intervention, in accordance with ethical principles.

The program logic model developed based on the participatory ergonomic approach is presented in Fig. 2. The model provides an explanation of the study phases, the conceptual framework of participatory ergonomic approach and how it is implemented, the health promotion training program, and the process used to assess the expected outputs.

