*The use of a mixed-methods protocol to identify risk factors:* Housework refers to a series of routine activities done by a person during the day. Thus, housewives are exposed to multiple psychosocial and biomechanical risk factors. To the best of our knowledge, to date no study has been conducted to identify the multiple psychosocial and biomechanical risk factors that account for musculoskeletal disorders among housewives to design an educational intervention program for the target population. As such, psychosocial stressors will be identified in this study using in-depth and face-to-face interviews. Besides, using the JSA method, the living and work environments of housewives will be assessed, and the most important biomechanical risk factors will be identified. Accordingly, a training intervention program that is bespoke to the population of housewives under study will be implemented.*The use of a multidisciplinary (biomechanical and psychosocial) method to implement health promotion training programs:* Based on the reviews that have been done by the research team, the few studies that have been conducted to reduce musculoskeletal disorders in housewives have focused on only one of the known risk factors. However, we know there is a multiplicity of risk factors, so there is now a need to conduct a study using comprehensive interventions in this target group. Numerous studies have shown the interactive effects of biomechanical risk factors such as poor physical conditions and workload, and psychosocial risk factors such as lack of support from others have concluded that the interactive effect of risk factors underlying musculoskeletal disorders is broader than the effect of each risk factor alone. Thus, the present study will examine the gap in the literature to find out whether multidisciplinary interventions are more effective in reducing musculoskeletal disorders among housewives than biomechanical or psychosocial interventions performed separately. Accordingly, four separate groups will be evaluated in this study. This being so, we will be able to deduce which of these interventions is most effective in reducing musculoskeletal disorders.*Performing a randomized controlled trial:* This study will be the first randomized controlled trial performed on housewives to evaluate the effectiveness of comprehensive and multifaceted interventions. Randomized controlled trial designs are held as the gold standard, with best internal validity and least distortion in clinical interventions and healthcare. However, they have rarely been used to evaluate the effectiveness of intervention programs in informal work environments such as the home and housewives’ communities. The evaluations of this study will show that these interventions are possible and feasible in work environments, including the home environment.*The use of participatory ergonomics to implement the intervention program:* Using participatory ergonomics is another high-quality contribution of this study, as this technique engages end-users in the entire study process. According to the principles of this ergonomic approach, improving the health literacy level of housewives will increase their motivation and participation in intervention programs and afford more effective implementation. In addition, the use of network communications and facilitator training in the present study can significantly affect the effectiveness of interventions [30, 31].*Follow-up period:* The gap in the majority of intervention studies is that they have focused on short-term results. The present study explores the effectiveness of the training intervention over a longer period: collecting data at three time points: before the intervention (baseline) and follow-up 3 and 6 months after the intervention.

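### One facilitator forum spanning all three intervention arms opens an avoidable contamination route between the single-programme arms and the combined arm

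*Protocol article*

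**What the plan says.** All of this is in the protocol article, mostly under The intervention programs.

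- **Structure.** Each intervention arm of 40 is split into four subgroups of ten. "There will be an expert, as a facilitator, who will each manage one of the 12 subgroups, overseen by a coordinator".
- **Contact with participants.** Each subgroup meets every week to go over the taught material again and to talk through what its women have done. Facilitators also review with their women the training that their subgroup was given.
- **Exchange between facilitators.** "The facilitators of the intervention groups will communicate with each other by forming a social group through virtual networks and face-to-face meetings", and they will "share the experiences of their subgroups with each other". No limit to facilitators of the same arm is stated.
- **Restraints.** It will be made clear that "facilitators should not interfere in the participant’s training procedures or in the implementation of the interventions". The coordinator checks that subgroup training and interactions are appropriate and will "intervene if necessary, to reduce any foreseeable risk of harm".
- **What separates the arms.** "The multidisciplinary groups will receive both of the other two interventions in full". The combined arm therefore differs from each single arm by one component.
- **The comparison at stake.** The end of the Background adds the hypothesis that the combined programme outperforms each separate one. The Discussion names as the gap to be filled "whether multidisciplinary interventions are more effective in reducing musculoskeletal disorders among housewives than biomechanical or psychosocial interventions performed separately".

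**The concern.** A comparison of the combined programme with one component tests the added value of the other component. It is interpretable only if women in the single-programme arms do not receive that other component. The plan sets up a regular channel between the people who deliver contact in all three arms, and those people then return to single-programme subgroups to go over content and actions. A facilitator in the biomechanical arm can hear what psychosocial and multidisciplinary subgroups are doing and bring it to her own group, and the reverse.

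The combined arm already has both contents, so leakage would run mainly into the single arms. These would come to resemble the combined arm, and each other. A finding of no difference would then have two explanations that the trial could not separate: no added benefit, or arms that had become alike.

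**Working it through.** **1. Does the route exist in the text?** Three statements are needed, and all are in the same section:

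- The forum is described in the singular, for facilitators of the intervention groups in the plural, with no restriction by arm.
- What is exchanged is the experience of the subgroups.
- Each facilitator then meets her subgroup weekly to go over material and actions.

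**2. Do the stated restraints close it?**

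| Restraint | What it covers | Bars another arm's content? |
|---|---|---|
| Non-interference | Training procedures and implementation | Not expressly |
| Review of what the subgroup was taught | Describes the facilitator's task | Not expressly; the same meetings also discuss experiences and actions |
| Coordinator oversight | Appropriateness of training and interactions; stated aim is risk of harm | Not expressly |

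**3. Which comparisons are exposed?** Combined versus each single arm, and biomechanical versus psychosocial. The control arm has no subgroups or facilitators, so intervention versus control is not diluted by this route.

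**4. The plan's own sample size first.** Inputs from Sample size and power calculations: SDs 20.2 and 21.1, difference 15, z-values 1.96 and 0.84.

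n = (1.96 + 0.84)² × (20.2² + 21.1²) / 15² = 7.84 × 853.25 / 225 = 29.73, rounded up to 30.

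The article prints 29.9 and also rounds to 30, so its figure reproduces.

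**5. Illustration of dilution.** Two inputs are assumptions: the true contrast is 15 points, and a share L of it is lost through leakage, so that 15(1 − L) remains.

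- Common SD = √((20.2² + 21.1²)/2) = √426.625 = 20.65
- Standard error with 30 per arm = 20.65 × √(2/30) = 5.33
- Power = Φ(15(1 − L)/5.33 − 1.96)

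| Assumed L | Remaining contrast | Power, 30 per arm |
|---|---|---|
| 0% | 15 | 0.80 |
| 10% | 13.5 | 0.72 |
| 20% | 12 | 0.61 |
| 30% | 10.5 | 0.50 |
| 40% | 9 | 0.39 |

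**6. Sensitivity to the starting contrast.** The article does not say that 15 points is the combined-versus-single difference. If that difference were 7.5 points (assumed), power would be Φ(7.5/5.33 − 1.96) = 0.29 with no leakage at all. Dilution would then fall on a comparison that is already weak.

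**The case against.** The case against has real substance.

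- **Training is arm-specific first.** Subgroups begin after each arm has had its own programme. Leakage would be second-hand and would need a facilitator to step outside her stated role. This stands, and it makes large leakage less likely. It does not remove the route.
- **Restraints exist.** The three listed above could reduce leakage in practice. This stands too, but none is framed as protection between arms.
- **Experiences are not content.** The article speaks of sharing subgroup experiences, not teaching material. That is correct. However, what a subgroup does in response to its programme is hard to describe without conveying some of the programme.
- **The network is deliberate.** The Discussion presents network communication and facilitator training as able to influence effectiveness. Splitting the forum is therefore a trade-off.
- **This is a condensed article.** A facilitator manual may contain separation rules. The point does not rest on a missing rule, however. It rests on a stated procedure that, as written, crosses arms.

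A reader might also infer more than the documents support:

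- *That the arms will be contaminated.* The text shows a route, not an effect.
- *That the trial's main hypothesis is compromised.* The Background first hypothesises benefit over control and then adds the combined-programme hypothesis. The listed primary outcomes are model selection and intervention design, with effectiveness secondary.
- *That power for combined versus single is 0.80 and falls from there.* The 15 points follow a cited trial in office workers and are not tied to this contrast.
- *That the weekly reminders are shared between arms.* The article says only that they go through a virtual network.
- *That recruiting from one city is part of this problem.* It would be a participant-to-participant route, which separating facilitators would not address.

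**Conclusion.** The point holds as a foreseeable design risk with a simple remedy. As written, facilitators of all three intervention arms share subgroup experiences in one forum while working weekly with single-programme subgroups, and no stated restraint expressly bars carrying content over. Any leakage would push combined versus single, and biomechanical versus psychosocial, towards no difference.

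Its size cannot be derived from the documents. The fall in power to 0.61 or 0.39 rests on an assumed 20% or 40% dilution, an assumed 15-point contrast, proportional loss and 30 analysed per arm. It shows how sensitive such a comparison would be and is not an estimate for this trial. The point is a cheap improvement, not a flaw that invalidates the design.

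**What to change.** 1. Hold facilitator exchange, both online and face to face, within each arm. Alternatively, allow cross-arm exchange on process matters only, such as attendance, scheduling and running a group.
2. Let only the existing coordinator see across arms.
3. Add to facilitator training that content from another arm must not be introduced in subgroup meetings.

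**Cost.** Three facilitator groups in place of one, with separate face-to-face meetings, and one added instruction in training. No extra staff are needed, since the coordinator role already exists. Allocation follows the completion of recruitment, so the change can be made before subgroups start. The downside is less exchange of experience between arms, which the authors regard as a strength; the process-only option keeps part of it.

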**Fig. 2 Fig2:**
[figure not shown]
The program logic model for the participatory ergonomic approach (adapted from Haines & Wilson) [30, 31]

### Instruments

The instruments that will be used to collect the data are the Rapid Entire Body Assessment (REBA) [32], the Visual Analog Scale (VAS) [33], the Work Ability Score (WAS) [34], the Hospital Anxiety and Depression Scale (HADS) [35], and the 36-item Short-Form Health Survey (SF-36) [36]. Table 3 presents the general features of the mentioned instruments.

**Table 3 Tab3:** Summary of the instruments used for data collection

Scale	Content	Scoring
VAS	Pain intensity	0 (no pain)–10 (severe pain)
REBA	The Rapid Entire Body Assessment	1 (no need for assessment), 11––15 (immediate assessment is required)
WAS	Work ability	0 (inability to perform activities)–10 (ability to perform activities)
HADS	The Hospital Anxiety and Depression Scale	0 (lowest anxiety/depression level)–21 (highest anxiety/depression level)
SF-36	Health-related quality of life	7 subscales: 0 (the worst)–100 (the best)

### Sample size and power calculations

Following the study conducted by Shariat [37], which similarly used a three-arm, parallel, RCT to investigate MSDs in office workers, the sample size we require in the quantitative phase to provide ample power was calculated as 30 persons for each group. This sample size was calculated to be sufficient at an alpha of 0.05 and a power of .80, to test for a difference between the groups. Nevertheless, sample size calculations are sensitive to error and complicated when drawing upon incomplete information in the literature [38]. Additionally, experience indicated we must consider a potential dropout rate of 30%. Hence, according to the following formula, we should work with an initial recruitment target of 40 participants in each group:
$$ n=\frac{{\left({Z}_{1-\frac{\alpha }{2}}+{Z}_{1-\beta}\right)}^2\left({\delta_1}^2+{\delta_2}^2\right)}{{\left(\overline{{\overline{X}}_1}-{\overline{X}}_2\right)}^2}=\frac{{\left(1.96+0.84\right)}^2\left({20.2}^2+{21.1}^2\right)}{{\left(-15\right)}^2}=29.9\cong 30 $$

N=30+30(0.3)≅40

In line with this approach, a total of 160 housewives aged 20–65 years with WMSDs will be recruited based on the health records available in the health centers of Akbarabad-Kavar city by taking into account the inclusion and exclusion criteria given in Table 1. Participants will be allocated into four groups (the three intervention groups plus one control group) based on permuted block randomization. The allocation is concealed by using opaque, sealed envelopes that are consecutively numbered and included each group’s name. Sampling using this randomization process gives each participant an equal chance of being placed in each group [39].

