### Data analysis

#### Phase 1

To perform the process of qualitative content analysis, the audio file of each interview will be listened to attentively several times on the same day and it will be transcribed verbatim. To keep the data from the interviews confidential, a code will be assigned to each transcript. To come up with a general impression of the interviews and become fully immersed in the data, the audio files of the interviews and the transcripts will be reviewed several times, and any possible ambiguities and inconsistencies will be removed by comparing the audio files and the transcripts. The interviews will be audiotaped and a summary of the key issues in each interview will be then sent to each participant to ensure that the researcher will have accurately interpreted that participant’s comments (a “member check”) [26]. The process of data analysis will be performed continuously and simultaneously with the data collection process. All words, sentences, and paragraphs that are related in the analysis process will be considered as a single semantic unit. After merging the semantic units, the codes will be extracted. The codes together form the subcategories and then the main categories. Finally, upon the abstraction of the categories, the relevant themes will be identified. MAX.QDA software will be used to manage the data [40].

#### Phase 2

The collected data will be analyzed with SPSS software using descriptive statistics (including frequency, frequency percentage, mean, and standard deviation) and inferential statistics. We will undertake both “intention to treat” and “per protocol” approaches to the inferential statistical analyses to achieve fully understand the outcomes and manage bias in the face of any drop out. To compare the differences between the values obtained before the intervention and 3 and 6 months after the intervention in each group, generalized mixed models of analysis of variance for repeated measures will be used. We will also calculate differences between means of the independent groups with their respective 95% confidence intervals. All tests will be performed at a significance level of 0.05 (p <0.05). The Kolmogorov-Smirnov test will be used to test the normality of the data. The per protocol analyses will only include the participants who complete the intervention to which they were allocated.

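### The 30% dropout allowance is added to the required 30 instead of divided out, so 40 per group gives about 78% power, not 80%, if the assumed dropout occurs

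*Protocol article*

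**What the plan says.** All the figures stand in the protocol article under Sample size and power calculations. The size for the quantitative phase "was calculated as 30 persons for each group", judged sufficient "at an alpha of 0.05 and a power of .80, to test for a difference between the groups". The printed formula compares two means, with standard deviations 20.2 and 21.1, a difference of 15 in absolute value, and normal quantiles 1.96 and 0.84. Its printed result is 29.9, taken as 30.

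The section then turns to attrition: "experience indicated we must consider a potential dropout rate of 30" per cent. It concludes that "we should work with an initial recruitment target of 40 participants in each group". The line below the formula shows how: 30 plus 30% of 30, set approximately equal to 40. With four groups, "a total of 160 housewives aged 20–65 years with WMSDs will be recruited".

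Under Data analysis, Phase 2, the article plans both intention-to-treat and per-protocol analyses, with mixed models for repeated measures. On the second population it says: "The per protocol analyses will only include the participants who complete the intervention to which they were allocated".

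**The concern.** The number to recruit must be such that, after the assumed share of recruits is lost, the required number is left. The plan takes 30% of the number it needs at the end, not 30% of the number it enrols. That always falls short: n × (1 + d) is below n/(1 − d) for any dropout d above zero. Rounding 39 up to 40 recovers part of the shortfall but not all of it.

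The article presents 40 per group as the number that follows from needing 30 and expecting to lose 30%. If it does not follow, a reader who later has to interpret a null result will credit the trial with slightly more power than its own assumptions give.

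**Working it through.** **Inputs**, all from Sample size and power calculations: two-sided alpha 0.05 (z = 1.96); power 0.80 (z = 0.84); SDs 20.2 and 21.1; difference 15; dropout 30%; 40 recruited per group, four equal groups.

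**1. The plan's own figure for those completing.**
- Sum of variances: 20.2² + 21.1² = 408.04 + 445.21 = 853.25.
- n = (1.96 + 0.84)² × 853.25 / 15² = 7.84 × 853.25 / 225 = 29.73.
- This rounds up to 30, as in the plan. The article prints 29.9 for the same expression; the rounded result is the same.

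**2. The plan's own figure for those recruited.**
- 30 + 30 × 0.3 = 39, printed as 40. The plan's number is reproduced by this additive rule with rounding up.

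**3. What 40 leaves at the assumed dropout.**
- 40 × (1 − 0.30) = 28, which is 2 short of 30.
- Number needed to keep 30: 30 / 0.70 = 42.9, so 43 per group (43 × 0.70 = 30.1).
- Total: 4 × 43 = 172, against 160. The difference is 3 per group, 12 in all.

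**4. The dropout that 40 can absorb.**
- 1 − 30/40 = 0.25. Up to 25% loss, at least 30 per group remain.

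**5. Power with the plan's inputs.** Normal formula: Φ(15 / √(853.25/n) − 1.96).
- n = 30: 15 / √28.44 = 2.813, and Φ(0.853) = 0.803.
- n = 28: 15 / √30.47 = 2.717, and Φ(0.757) = 0.776.

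The same comparison with the noncentral t distribution (common SD √(853.25/2) = 20.65):

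| Completers per group | Normal formula | t test |
|---|---|---|
| 30 | 0.803 | 0.790 |
| 28 | 0.776 | 0.761 |

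Like for like, losing 2 women per group costs 0.803 − 0.776 = 2.7 points by the normal formula and 0.790 − 0.761 = 2.9 points by t test. Against the nominal 0.80, the plan's own method falls short by 2.4 points.

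**6. The same gap as a detectable difference.** With 28 per group, 80% power is reached at 2.8 × √30.47 = 15.5 points instead of 15.

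**The case against.** The best defence has four parts.

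*The 80% belongs to 30 per group, and 30% is only a potential rate.* This is true. The article attaches its power to 30 women, not to 28, and the limitations paragraph of the Discussion expects attrition to be low. A reader might infer that 80% power, 30% dropout and 40 per group cannot all be stated together, or that the trial is underpowered whatever happens. The document does not support that: at 25% dropout or less, 40 per group is enough. What remains is that the section offers 40 as its answer to a 30% loss, and for a 30% loss it is not the right answer.

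*The mixed model can use partial data.* This stands in part. A woman lost after the 3-month visit can still contribute to the intention-to-treat analysis, so 28 may understate the information available there. But the sample size formula is a plain comparison of two means and takes no credit for repeated measures, and the per-protocol analysis rests on completers.

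*The t-test figure exaggerates.* Setting 0.761 against 0.80 would indeed mix two effects, because the t test gives only 0.790 at the full 30 per group. The fair comparison is 0.790 with 0.761.

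*The difference between 29.9 and 29.7 is not a proven error.* The printed inputs may be rounded: SDs of 20.25 and 21.15 would give 7.84 × 857.39 / 225 = 29.87, and a difference of 14.96 with the printed SDs would give 29.89. It deserves a check, no more; both values round up to 30.

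A reader might also want to add the effects of the subgroup format or of several between-group comparisons to this shortfall. They are separate questions. Nothing in this calculation sizes them, and the point does not rest on them.

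**Conclusion.** The dropout allowance is wrong as written. On the plan's own inputs, 40 per group with 30% lost leaves 28 completers, and power for the 15-point difference is about 78% by the plan's normal formula instead of 80% (76% against 79% by t test). The correct inflation would be 43 per group.

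The effect is small and conditional. It appears only if dropout exceeds 25%, and it amounts to 2.4 points below the nominal power if dropout reaches 30%. The result assumes equal loss in the groups compared, an analysis of completers, and the printed SDs and difference. It does not threaten the trial's validity and gives no reason to enlarge it. It does mean that the printed justification claims slightly more than its assumptions deliver.

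**What to change.** Keep 160 women, which also fits the plan to split each intervention group of 40 into four subgroups of ten. Replace the inflation line and its conclusion with a statement such as: recruiting 40 per group leaves at least 30, and hence 80% power by the normal formula, provided dropout is at most 25%; at 30% dropout 28 remain and power is about 78%. If t-test figures are quoted, give both 79% at 30 per group and 76% at 28.

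In the same edit, check the printed 29.9 against the unrounded inputs. The printed ones give 29.7, and nothing depends on it.

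The cost is one corrected sentence and a slightly less favourable power figure. Recruitment, conduct and analysis do not change.
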